## Abstract

While regulations have restricted the sale of pod-style fruit-flavored e-cigarettes, observational and clinical data suggest that their use is associated with smoking cessation among adults. Surprisingly, no randomized clinical trials have tested whether fruit flavors affect smoking outcomes compared with those authorized for sale, and, if so, why. Adults who smoke cigarettes daily, who have had multiple prior unsuccessful quit attempts, and who are interested in quitting smoking by switching to an e-cigarette will be recruited. Eligible adults will be randomized to fruit, menthol, or tobacco-flavored e-cigarettes. The baseline smoking rate will be established on days 1-5. Laboratory visits on days 6 and 7 will assess flavor-associated subjective reward and the reinforcing value of flavored e-cigarettes relative to combustible cigarettes. Participants will then receive an e-cigarette device and a 6-week supply of nicotine pods (5% nicotine) in their assigned flavor, and a structured action plan to quit smoking by switching to the e-cigarette. The primary outcome is the longitudinal daily cigarette count from baseline through the end of the six-week switch period (primary endpoint) and at the 26-week follow-up (secondary endpoint). Complete switching will be verified with a carbon monoxide value < 5 ppm. Secondary outcomes include subjective reward, relative reinforcing value, and positive affect. This trial will determine if fruit-flavored e-cigarettes facilitate initial and sustained switching more than menthol or tobacco, whether greater rewarding and positively reinforcing effects drive switching, and if the unavailability of fruit-flavoring may foster continued smoking for those unable to quit with FDA-approved medication.

This trial was registered at CT.gov (NCT06264154) https://clinicaltrials.gov/study/NCT06264154 on February 16, 2024.

## Introduction

1

Nearly 70% of adults who smoke cigarettes (AWS) want to quit smoking [1], and 55% report trying to quit at least once in the past year, yet over 90% fail [2], despite using smoking cessation medication [1]. Indeed, the average smoker will attempt to quit smoking at least 30 times before abstaining for 12 months or longer [3,4]. These attempts typically occur over decades of smoking, carcinogen and toxicant exposure, resulting in 480,000 deaths annually [5,6].

As highlighted in the Surgeon General's Report [5], helping AWS who cannot quit smoking switch to less harmful noncombustible nicotine-containing products, such as e-cigarettes [[7], [8], [9], [10], [11], [12], [13], [14], [15], [16]], has the potential to reduce this health burden dramatically [5,7,16]. Substituting e-cigarettes for combustible cigarettes might only be possible for AWS persistently if e-cigarettes are accessible and appealing [7]. The Food and Drug Administration banned the sale of flavored pod-style e-cigarettes, other than tobacco and menthol, given their appeal to youth [17]. Harm reduction proponents have advocated for the continued availability of e-cigarette flavors to appeal to and aid AWS who have been unable to quit with traditional methods [7,18,19]. Yet there are no prospective studies of the effect of flavor on initial and sustained switching from combustible to electronic cigarettes.

Converging lines of research provide a strong scientific premise for a prospective investigation of the role of fruit flavor in the substitutability of e-cigarettes for combustible cigarettes among AWS persistently. Survey studies have observed greater fruit-flavored e-cigarette use among AWS who fully substituted e-cigarettes for combustible cigarettes [20]. Clinical trials of tobacco/menthol-flavored e-cigarettes for smoking cessation have shown modest or short-lasting effects [21,22], while a trial where AWS predominantly self-selected fruit flavors showed long-lasting effects of e-cigarettes versus nicotine replacement [18].

According to Behavioral Economic Theory, e-cigarettes will substitute for combustible cigarettes if they have comparable reinforcer efficacy [23,24], meaning they must be subjectively rewarding, relatively reinforcing, and capable of increasing positive affect [7]. Research suggests that through these mechanisms, fruit-flavored e-cigarettes may enhance the substitutability of e-cigarettes for combustible cigarettes among AWS. First, the sweetness of fruit flavors has the largest effect on subjective reward [25], and subjective reward increases as the concentration of fruit flavor increases [26]. Second, fruit-flavored e-cigarettes are vaped longer, more deeply, and more frequently than other e-cigarette flavorings [23,27,28]. Third, fruit-flavored e-cigarettes enhance nicotine's rewarding and reinforcing effects in smokers [23,29] compared to non-fruit-flavored e-cigarettes. Finally, e-cigarettes with fruit flavoring, especially one's brand, increase positive affect [27], and use maintains positive affect among abstinent AWS [30,31].

## Aims and hypotheses

2

The current study (NCT06264154) has two aims. Aim 1 seeks to evaluate the effects of fruit-flavored versus tobacco-flavored and menthol-flavored e-cigarettes on combustible cigarette smoking among adults who have persistently smoked. We hypothesize that participants randomized to fruit-flavored e-cigarettes will be more likely to switch from combustible cigarettes to e-cigarettes during the 6-week switch phase and at the 26-week follow-up than participants randomized to tobacco-flavored or menthol-flavored e-cigarettes. Complete switching, partial switching, and no switching will be measured. Aim 2 seeks to examine whether the rewarding and reinforcing effects of e-cigarette flavoring mediate switching behavior. We hypothesize that fruit-flavored e-cigarettes will produce greater subjective reward, relative reinforcing value, and positive affect than tobacco-flavored or menthol-flavored e-cigarettes. In turn, greater subjective reward, relative reinforcing value, and positive affect will predict fewer cigarettes smoked per day during the 6-week switch phase and at the 26-week follow-up.

## Methods

3

### Overview of study design

3.1

The proposed study will evaluate whether fruit-flavored (FF: watermelon and blueberry) versus traditional-flavored e-cigarettes [tobacco (TF) or menthol (MF)] more readily substitute for combustible cigarettes and if the rewarding and reinforcing effects of flavoring facilitate changes in smoking behavior among 210 adults who have persistently smoked cigarettes. Eligible adults will be randomly assigned 1:1:1 to FF (n = 70), TF (n = 70), or MF (n = 70) and participate in 9 visits across 26 weeks (see Fig. 1). Baseline cigarette smoking rate will be established over days 1-5. After overnight smoking abstinence, a laboratory visit on day 6 will assess e-cigarette flavor-associated subjective reward, affect, craving relief, and withdrawal relief. After overnight smoking abstinence, a laboratory visit on day 7 will assess the reinforcing value of the assigned e-cigarette flavor relative to combustible cigarettes.

**Fig. 1 fig1:**
[figure not shown]
Overview of study design.

Participants will then receive instructions and an action plan to switch to e-cigarettes for the following 6 weeks (weeks 2-7). Participants will collect their used cigarette filters and their used e-cigarette pods daily to assess consumption of cigarettes per day (CPD) and pods per day (PPD). The primary outcome will be the longitudinal daily count of cigarettes from baseline to the end of the 6-week e-cigarette switch phase. A secondary endpoint will be cigarettes per day from week 8 to week 26, measured by timeline-follow-back (TLFB). Complete switching will be verified with a carbon monoxide (CO) value < 5 ppm. Secondary outcomes include subjective reward, relative reinforcing value, and positive affect. The protocol was approved by the University of Pennsylvania's Institutional Review Board (854051) and participants provided written informed consent.

### Participant eligibility

3.2

Study participants (≥21 years old) will be 210 male and female adults who have persistently smoked cigarettes and are motivated to switch from combustible cigarettes to e-cigarettes. Persistent smokers are defined as those who have repeatedly tried to quit and failed to quit, even with the use of smoking cessation medication. To be eligible, potential participants must: (1) be English speaking; (2) report having smoked at least 5 cigarettes per day for the past 6 months and ever use of an e-cigarette; (3) have a CO ≥ 10 ppm; (4) be willing to switch to e-cigarettes for 6 weeks and use the assigned flavors.

Exclusion from study participation will be warranted due to: (1) regular use of any nicotine-containing products other than cigarettes; (2) regular e-cigarette use defined as ≥ 5 days/30 days; (3) current or impending (during study period) enrollment in a smoking cessation program; (4) current use of smoking cessation medication; (5) allergies to either propylene glycol or flavor additives; (6) current use of recreational drugs (other than nicotine and cannabis), current treatment for substance use, and alcohol use exceeding 20 standard drinks per week; (7) current or planned pregnancy or lactation; (8) history or current diagnosis of psychosis; and (9) serious or unstable disease in the past year (e.g., cancer, cardiovascular event).

### Participant recruitment and screening (Day 0)

3.3

AWS will be recruited from the community through social media advertisements. Those who respond to the ads will undergo phone prescreening to determine whether they meet the inclusion and exclusion criteria. Interested and initially eligible adults will attend an Intake Visit to confirm final eligibility. After providing informed consent, eligibility will be verified by a negative pregnancy test for females of childbearing potential, a negative urine drug screen, and a CO level >10 ppm. Those who qualify will complete baseline assessments, including demographics, smoking history, e-cigarette use history, nicotine dependence, and depression and anxiety symptoms.

### Baseline smoking assessment (Week 1, days 1-5)

3.4

Participants will be instructed to smoke as usual on days 1-5. They will receive five date-stamped zipped baggies [32,33]. A written instruction card for collecting and storing spent cigarette filters will be reviewed with each participant. Participants will collect all spent filters through day five and receive a monetary incentive ($35) to return the baggies [32,33]. Participants will return used cigarette filters in the date-stamped zipped baggies at the day 6 laboratory visit. Participants will be randomized to fruit, tobacco, or menthol-flavored e-cigarettes in an unblinded manner, with the computerized allocation sequence generated by the biostatistician and accessible only to the data manager. Randomization will be stratified by sex, nicotine dependence, depression/anxiety, and menthol cigarette status.

### Laboratory assessments

3.5

#### Flavor-associated subjective reward and positive affect (Day 6)

3.5.1

Participants will attend a laboratory session after overnight smoking abstinence (10 h; CO verified <10) on day 6 [23,34]. Cigarette craving, withdrawal symptoms, and positive and negative affect will be measured before e-cigarette exposure. They will receive instructions on how to use the e-cigarette before two e-cigarette exposures based on their flavor group assignment. On day 6, the traditional flavor groups will receive either two exposures of tobacco or two exposures of menthol flavoring, depending on their assignment. The fruit flavor group will receive blueberry and watermelon in a counterbalanced order. All exposures will have the same characteristics, only differing by flavor. Participants will take 14 puffs for the first exposure and 14 puffs for the second exposure. The exposures will be separated by 45 min [23,35]. After each exposure, participants will complete measures of subjective reward, craving, withdrawal, and affect. We chose to offer both watermelon and blueberry to participants randomized to fruit-flavored e-cigarettes to promote adherence if either flavor was unappealing. After this 1.25-h visit, participants will be compensated $40.

#### *R*elative reinforcing value of e-cigarette flavoring *(Day 7)*

*3.5.2*

Participants will arrive at their visit at 9:00 a.m. after abstaining from smoking overnight (10 h; CO-verified <10 ppm). Participants will receive an introduction to a validated behavioral choice paradigm that assesses motivation to use an e-cigarette in their assigned flavor category (fruit, tobacco, or menthol) relative to combustible cigarettes [23]. For those randomized to fruit flavoring, the aim is not to quantify the reinforcing value of the fruit flavors. The fruit flavor with the highest rewarding value (determined on Day 6) will serve as the fruit flavor for the relative reinforcing value of flavoring (RRVF) assessment.

The RRVF will be assessed by asking participants to “work” by moving a computer mouse to hit targets on one of two computer screens to earn points toward either e-cigarette puffs or cigarette puffs. Using a concurrent schedule [34,36], participants will be told that they can switch between the two screens as often as they wish. Participants are instructed to move the computer mouse so that the cursor hits the targets (e.g., either an electronic or combustible cigarette image) [23]. Consistent with relative reinforcement paradigms, the reinforcement schedule for the e-cigarette earning screen will remain constant at a fixed ratio FR-25 (25 targets achieved to earn a point). In contrast, the reinforcement schedule for the cigarette-earning screen will increase (require more effort) with a progressive ratio schedule of PR-25x over 10 trials, such that 25, 50, 75, 100, 125, 150, 175, 200, 225, and 250 targets will have to be achieved to earn a point [34,36,37].

The computer task will continue until a participant completes 10 trials and earns a total of 10 points, from which they will earn either one puff of an e-cigarette for each point (i.e., up to 10 puffs of an e-cigarette) or one puff of a cigarette for each point (i.e., up to 10 puffs of a cigarette). E-cigarette and/or cigarette puffs will be taken at the end of the procedure to prevent satiation from influencing responding in subsequent trials. RRVF is defined in relation to responding for cigarette puffs. The breakpoint is the highest trial that a participant is willing to work to earn a combustible cigarette puff and reflects the reinforcing value of cigarette smoking relative to e-cigarette vaping of the assigned flavor [23,37]. To ensure that responding is based on reinforcer preference rather than departure from the lab, the choice task will be followed by a 1-h wait in the laboratory. After completing this 2-h visit, participants will be compensated $45.

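### The 1-hour wait on Day 7 starts only when the choice task ends, so it reduces but does not remove the incentive to choose e-cigarettes in order to leave sooner

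*Protocol article*

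**What the plan says.** All of this is in section 3.5.2 of the protocol article, on the relative reinforcing value of flavoring (RRVF).

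- **Purpose of the wait:** "To ensure that responding is based on reinforcer preference rather than departure from the lab".
- **Rule adopted for that purpose:** so that preference drives responding "rather than departure from the lab, the choice task will be followed by a 1-h wait in the laboratory".
- **When the task ends:** "The computer task will continue until a participant completes 10 trials and earns a total of 10 points". No task duration is given.
- **Price of an e-cigarette point:** the schedule "will remain constant at a fixed ratio FR-25 (25 targets achieved to earn a point".
- **Price of a cigarette point:** it rises over the 10 trials, so that "25, 50, 75, 100, 125, 150, 175, 200, 225, and 250 targets will have to be achieved to earn a point".
- **Visit length:** arrival is at 9:00 a.m., and the section closes with "After completing this 2-h visit, participants will be compensated $45". It does not say that everyone leaves at the same time, or that the wait shortens when the task runs long.

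The score is the cigarette breakpoint, the highest trial at which a participant still works for a cigarette puff. Table 1 lists RRVF as a mediator. Sections 3.10.1 and 3.10.2 use it first as an outcome compared between flavor groups, then as a predictor of change in cigarettes per day.

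**The concern.** The protocol itself identifies wanting to leave as a threat to the measure and says that the wait deals with it. For that to be fully true, departure time must not depend on what the participant chooses. As written it does: departure is task end plus one hour, and task end depends on the choices.

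The incentive runs one way. E-cigarette points are never slower than cigarette points and soon become faster, so a participant who wants to go has a reason to stop working for cigarettes. That can lower the cigarette breakpoint for reasons unrelated to flavor. The relative value of the e-cigarette would then look somewhat higher in every arm. Individual differences in impatience would also enter a score meant to measure preference. What is at stake is the precision of RRVF as an Aim 2 group outcome, and the strength of its estimated relation to smoking.

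**Working it through.** **The plan's own figure for RRVF.** Section 3.10.1 gives a detectable breakpoint difference of 2.0 with 70 per group.

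- Implied SD of RRVF, from the standardized slope of 0.2, the change-score SD of 7.1 and the RRVF slope of 0.37: 0.2 × 7.1 / 0.37 = 3.84.
- Detectable standardized difference at 80% power, taking the two-sided 2.5% level stated for Aim 1 to apply here too: (2.241 + 0.842) × √(2/70) = 0.521.
- 0.521 × 3.84 = 2.0.

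The figure reproduces and is not in dispute. It is used below only as a scale.

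**Work by choice.** Inputs from section 3.5.2: 25 targets for each e-cigarette point, 25, 50, …, 250 targets for successive cigarette points, and 10 points in all. With k cigarette points, taking the k-th to cost 25k targets:

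targets(k) = 25 × k(k+1)/2 + 25 × (10 − k)

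| Cigarette points k | Targets | Ratio to minimum |
|---|---|---|
| 0 or 1 | 250 | 1.0 |
| 4 | 400 | 1.6 |
| 5 | 500 | 2.0 |
| 6 | 625 | 2.5 |
| 8 | 950 | 3.8 |
| 10 | 1,375 | 5.5 |

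**What the wait does to departure.** Departure(k) = task start + targets(k) × seconds per target + puffs + 1 h. For two choice patterns the 1 h appears on both sides and cancels. With puffing time taken as equal, the difference in departure is the difference in task time.

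**Size in minutes.** The article gives no response rate, so 0.5, 1 and 2 seconds per target are assumptions.

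| Contrast | Extra targets | 0.5 s | 1 s | 2 s |
|---|---|---|---|---|
| 0 v 10 cigarette points | 1,125 | 9.4 min | 18.8 min | 37.5 min |
| 8 v 10 | 425 | 3.5 min | 7.1 min | 14.2 min |
| 4 v 6 | 225 | 1.9 min | 3.8 min | 7.5 min |

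The last two rows span two points, which is the breakpoint difference the trial is powered to detect. The time cost is modest in mid-range and steeper at high breakpoints.

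**With a fixed release time.** If everyone leaves at the same interval after arrival, and the task and puffs fit within it, every entry in the table becomes 0.

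Minutes cannot be converted into breakpoint units, because nothing in the article says how strongly participants respond to earlier release.

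**The case against.** Five points can be made for the plan as written.

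1. **The wait does something useful.** Participants arrive after overnight abstinence, and the plainest threat is rushing the task to get out and smoke. A mandatory hour removes immediate release and makes any time saved a smaller share of the stay. This stands: the purpose is partly met. It does not amount to independence from departure, which is what the stated purpose claims.

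2. **A 9:00 a.m. arrival and a 2-hour visit may mean a fixed end.** An hour for the CO check, introduction, task and puffs, followed by an hour's wait, fits those figures, and an article may leave release details to the full protocol. The text does not exclude this, but it does not state it either. A task of variable length plus a constant hour does not give a constant 2 hours, and the Day 6 section uses a 1.25-hour visit length in the same nominal way. If a fixed stay is intended, saying so settles the point.

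3. **Work is the intended price of a cigarette puff.** This is correct, and the schedule itself is not criticized. Earlier release is a separate consequence, and one the protocol says it excludes.

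4. **The largest gaps use extremes and an assumed rate.** This also stands. At 2 seconds per target, 1,375 targets would take about 46 minutes and leave only 14 minutes of the first hour for everything else, so the upper end of the range may be unlikely.

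5. **The arms are treated alike.** A reader might infer that the flavor comparison on RRVF is confounded. The documents do not support that. The schedule, end rule and wait are the same in every arm, and assignment is randomized and stratified (section 3.4), so impatience is balanced in expectation. A reader might also infer that the path from RRVF to smoking is confounded. That is possible, because RRVF is not itself randomized, but nothing in the article links impatience to change in smoking.

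**Conclusion.** The point holds in limited form. A constant wait that begins at task end cannot make departure independent of choice when task work varies 5.5-fold with choice. The wait weakens the incentive to choose e-cigarettes in order to leave; it does not eliminate it.

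The likely consequence is some lowering of cigarette breakpoints in all arms, with noise or attenuation in RRVF, which is one of three Aim 2 mediators. It would be too strong to say that the score is known to be contaminated, or that the wait fails altogether. The Aim 1 primary outcome and the sample size are unaffected.

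The conclusion rests on reading section 3.5.2 literally, with the hour counted from the end of the task and the 2-hour length nominal. The minutes rest on the assumed response rates. On size alone this is a modest matter; it is worth acting on because the correction is nearly free.

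**What to change.** In section 3.5.2, replace the fixed 1-hour post-task wait with a release time fixed from arrival and the same for everyone, for example the end of the stated 2-hour visit. The wait then fills whatever remains after the task and the puffs. Add one line to the participant instructions, given before the task, saying that choices do not change when the participant leaves. If a fixed release is already the practice, stating it is enough.

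The cost is one procedural sentence and one instruction line. Fast finishers may wait somewhat longer. The task, schedule, score and analysis stay as they are. If some participants have already been tested under the present rule, record the date of the change so that RRVF scores before and after it can be told apart.

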### Switching intervention

3.6

#### E-cigarettes

3.6.1

We propose to use the NIDA Standardized Research Electronic Cigarette (SREC) for Clinical Research, manufactured by NJOY, LLC. The latest version of the SREC is a USB rechargeable closed device with a 400mAh battery permitting ∼200 (3-s) puffs per charge. The user cannot adjust the voltage or temperature settings. This pod-based system uses sealed pods pre-filled with 1.9 mL of e-liquid containing 5% nicotine by weight. Each pod provides ∼300 puffs. The e-liquid has a 0.77 PG/VG ratio and comes in four flavors: rich tobacco, menthol, blueberry, and watermelon. The pharmacokinetic profile of SREC is comparable to other pod-style e-cigarettes on the market (e.g., JUUL), which have been shown to deliver nicotine efficiently, similar to combustible cigarettes [[38], [39], [40]]. The SREC produces a consistent and characterized aerosol and was designed to serve as the standard for NIH clinical studies with human subjects.

